### Interim analyses {21b}

This is not applicable. No interim analyses will be conducted because all follow-ups occur at 6 months post-randomization and therefore will not inform intervention modification or discontinuation. The sponsor or chief investigator may prematurely discontinue the trial due to new safety information, lack of recruitment, or other reasons approved by the data monitoring committee (DMC), trial steering committee (TSC), regulatory authority, or ethics committee.

### Methods for additional analyses (e.g. subgroup analyses) {20b}

There are no planned subgroup analyses.

### Methods in analysis to handle protocol non-adherence and any statistical methods to handle missing data {20c}

Information on the time to return to EET will be collected throughout the follow-up period, up to 6 months after randomization. Secondary outcomes will be measured at 6-month follow-up and at baseline where specified. We will report the number and proportion of participants with complete data. If there is no published guidance on handling missing values for included measures of outcome, we will prorate the scales/subscales (i.e. calculate the average value of the complete items and use it to replace the missing values, if no more than 20% of the items are missing). Missing baseline data is not an issue for the primary analysis, as NHS Trust is the only covariate. If there are missing items at baseline for secondary outcomes, mean imputation may be applied, as recommended by White and Thompson [35]. The primary analysis of time/return to EET is expected to have relatively complete data, as the dates will be requested from clinical teams and institutions, rather than participant interviews. For secondary outcomes with > 10% missing data at 6-month follow-up, we will investigate baseline predictors of missingness and include them in adjusted models, such as conditioning or multiple imputation. Participants in both arms are expected to receive an adequate dose of treatment, although the implementation of TAU may vary between trusts.

### Plans to give access to the full protocol, participant level-data and statistical code {31c}

The full protocol is available on the funder’s website. To ensure comprehensive and transparent reporting of study findings, we will adhere to the CONSORT-SPI 2018 Extension reporting guidelines [36]. Participant flow through the study will be depicted using a CONSORT-SPI flow diagram, including the number of participants approached for enrolment, the decline rate, and assessments to confirm eligibility and outcomes between groups. To prevent selective reporting, all outcomes will be reported as specified in this study protocol. The study team will have exclusive use of the data until all planned primary and secondary analyses are published. After that, the anonymized quantitative dataset will be available from the corresponding author upon reasonable request.

## Oversight and monitoring

### Composition of the coordinating centre and trial steering committee {5d}

The trial management group (TMG) will consist of the chief investigator (CI), trial manager, research assistants, and trial statistician team. The CI, trial manager, and research assistants will meet weekly to ensure that the study is progressing according to the protocol, planned timelines, and budget. The trial steering committee (TSC) will be appointed and function according to HTA guidelines. The TSC will meet twice yearly to provide expert oversight and advice on all aspects of the trial. The TMG will prepare a report for the TSC.

### Composition of the data monitoring committee, its role and reporting structure {21a}

The DMC will be appointed and function according to HTA guidelines. The DMC will meet twice in the first and second years of the project and function according to HTA standard operating procedures. An independent chair and statistician will be appointed to the DMC. The DMC will monitor initial patient recruitment numbers (i.e. numbers recruited at the sites). The DMC will advise on recruitment difficulties and resource allocation.

### Adverse event reporting and harms {22}

Clinical teams will monitor safety throughout the study. Any unfavourable or unintended sign, symptom, or illness (AE) will be recorded, including exacerbations of pre-existing illnesses, increased frequency or intensity of pre-existing episodic events or conditions, conditions detected after randomization, and continuous persistent disease or symptoms present at baseline that worsen following randomization. Serious AEs (SAEs) include life-threatening events, death, inpatient hospitalization or prolongation of existing hospitalization, significant or persistent incapacity/disability, or pregnancy. We will report AEs from the signing of the study consent form to the last follow-up assessment 6 months after randomization. The chief investigator and an independent clinical reviewer will assess the causality and expectedness of SAEs. We will submit serious, related and expected (SAR) events to the DMEC/TSC and sponsor as needed. We will report all related and unrelated SAEs to the participant's NHS Trust and the REC as appropriate. We will also report any events rated as also unexpected (SUSAR) to the REC within 15 days of first notice.

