### Eligibility criteria {10}

Inclusion and exclusion criteria for study participants are detailed in Table 1.

**Table 1 Tab1:** Inclusion and exclusion criteria

Inclusion	Exclusion
1. Young people aged 12 years 0 months to 17 years 11 months (exclude if 18 at randomization) 2. Young people who can consent* and who are being considered for in-patient psychiatric admission or ICCS in the participating NHS Trusts. * Eligible participants under 16 years of age will require the consent of at least one person with parental responsibility	1. Local ICCS or TAU teams unable to accept new referrals due to their full capacity being reached. 2. Young people unable to consent due to their mental state. 3. The young person’s risk profile is incompatible with ensuring their safety and/or the safety of others in the community, as indicated by a Children’s Global Assessment Scale (CGAS) score of < 20

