## Interventions

### Explanation for the choice of comparators {6b}

Participants randomized to the control arm will receive TAU, which may include inpatient care delivered in the hospital or all other community CAMHS except ICCS. After the initial assessment, young people are treated with a combination of psychological, pharmacological, and/or social interventions as needed to achieve the goals set with their families. Treatment is not time-limited, but the average duration of treatment is about 50 days. Hospital treatment is followed by standard community treatment.

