## Discussion

Community-based treatment and inpatient admission are distinct models of care. The existing research is not sufficient to determine their relative effectiveness to enable evidence-informed policymaking and service planning. The IVY study is the only study to date with substantial potential to address the uncertainties in the true clinical and cost-effectiveness of ICCS as an alternative to inpatient admission. The IVY study is a definitive RCT in a real-life healthcare setting, at multiple sites with a representative geographical spread and a range of clinicians from diverse disciplinary backgrounds. We chose time to EET as the primary outcome measure because economic studies have shown that achieving both health and employment outcomes is necessary to generate better social and economic benefits for individuals and society [37]. This outcome measure is also compatible with the National Mental Health Service Dataset, making the trial results highly compelling to policymakers, healthcare providers, and mental health researchers. The trial results could lead to positive changes in clinical practice, such as developing new guidelines. The IVY study will evaluate ICCS's impact on a wide range of symptomatology and health outcomes experienced by young people with psychiatric emergencies, including self-harm, suicidality, general health, and well-being. The study will also provide accurate information about the services accessed under ICCS and TAU. A comprehensive cost-effectiveness evaluation will assess costs offset and costs saved by ICCS compared to TAU. Thus, the IVY study will provide unprecedented data on the relative clinical effectiveness, cost-effectiveness, and service utilization of ICCS and TAU for young people with psychiatric emergencies.

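### The SAE definition does not separate psychiatric admission given as care for the index crisis from admission caused by a new or worsened event, so SAE counts by arm can be confounded with treatment setting

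*Protocol article*

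**What the plan says.** The seriousness criteria are in Adverse event reporting and harms {22}: "Serious AEs (SAEs) include life-threatening events, death, inpatient hospitalization or prolongation of existing hospitalization". Lasting or marked disability and pregnancy complete the list. The same section sets the window: "We will report AEs from the signing of the study consent form to the last follow-up assessment 6 months after randomization". It describes the adverse events themselves broadly: "Any unfavourable or unintended sign, symptom, or illness (AE) will be recorded, including exacerbations of pre-existing illnesses". Baseline symptoms that get worse after randomization are also included. The chief investigator and an independent clinical reviewer then judge causality and expectedness.

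Three other sections show how close hospital admission lies to the treatments being compared:

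- Eligibility criteria {10}, Table 1, enrols young people "who are being considered for in-patient psychiatric admission or ICCS in the participating NHS Trusts".
- Explanation for the choice of comparators {6b} describes the control arm as "TAU, which may include inpatient care delivered in the hospital or all other community CAMHS except ICCS".
- The Discussion says the trial addresses the clinical effectiveness and "cost-effectiveness of ICCS as an alternative to inpatient admission".

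Intervention description {11a} adds that ICCS teams take part in hospital admissions, so admission can occur in either arm. Length of hospital stay is also a secondary outcome.

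**The concern.** In most trials, hospitalization is a reasonable marker of serious harm because it is not part of what is being compared. Here it is. Everyone enrolled is already a candidate for admission. Consent precedes randomization and event reporting starts at consent, so an admission for the index crisis after consent falls inside the reporting window. Under TAU that admission may simply be the care delivered. Under ICCS it may mean that the alternative to admission did not hold. The definition gives both the same label. Prolongation of a stay adds to this, since it can arise only in someone already in hospital.

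The safety question that matters most is whether treating high-risk young people in the community leads to more self-harm, life-threatening events or deaths. A total SAE count that also carries many treatment admissions can hide the answer. The count has uses beyond the final report: Criteria for discontinuing or modifying allocated interventions {11b} says that safety concerns from AEs and SAEs will lead to protocol amendments, and Interim analyses {21b} allows the trial to be stopped for new safety information.

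**Working it through.** The article states no SAE rate, admission rate or safety test, so there is no figure to reproduce. The check has two parts.

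**1. Does the text let a treatment admission count as an SAE?**

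- Seriousness: inpatient hospitalization and its prolongation are listed, with no exception.
- Window: from consent to the 6-month assessment, so an index admission after consent is covered.
- Entry condition: an SAE must first be an AE. An admission for a crisis that has not changed since consent is not clearly an unfavourable or unintended sign, symptom or illness. However, exacerbations and post-randomization worsening are named as AEs, and in an acute psychiatric crisis many admissions could be described that way.
- Later filter: causality and expectedness review classifies SAEs but does not remove them, and unrelated SAEs are still reported to the Trust and the ethics committee as appropriate.

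The text is therefore ambiguous. Two sites could classify the same admission differently, and both could defend it.

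**2. How large could the effect be?**

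Let *a* be the probability of psychiatric admission in an arm and *b* the probability of any other SAE. Treating the two as independent and counting every admission as an SAE:

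P(any SAE) = 1 − (1 − b)(1 − a)

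Both *a* and *b* are assumptions. With b = 10% in both arms:

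| Admission, TAU vs ICCS | P(SAE) TAU | P(SAE) ICCS | Ratio TAU/ICCS |
|---|---|---|---|
| 50% vs 20% | 1 − 0.90 × 0.50 = 55% | 1 − 0.90 × 0.80 = 28% | 1.96 |
| 80% vs 30% | 1 − 0.90 × 0.20 = 82% | 1 − 0.90 × 0.70 = 37% | 2.22 |
| 50% vs 40% | 55% | 1 − 0.90 × 0.60 = 46% | 1.20 |
| 30% vs 30% | 37% | 37% | 1.00 |
| 30% vs 50% | 37% | 55% | 0.67 |

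At the design size of 126 per arm (Sample size {14}), the first row corresponds to about 69 vs 35 participants with an SAE. A simple two-sided 5% comparison of those proportions would be significant about 99% of the time, although other harms are equal. For the same 50% vs 20% admission rates, b = 5% gives 52.5% vs 24% (ratio 2.19), and b = 20% gives 60% vs 36% (ratio 1.67).

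Dilution follows from the same formula. Suppose other SAEs were twice as common under ICCS, 20% against 10%, with admission again 50% vs 20%. TAU gives 55% and ICCS gives 1 − 0.80 × 0.80 = 36%. The total (0.55/0.36 = 1.53) would still appear to favour ICCS.

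If index-crisis admissions are shown separately by one rule in both arms, the remaining proportion is *b* in each arm. With equal *b* the ratio is 1.00 in every row of the table.

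**The case against.** A reader might infer that hospitalization is the comparator treatment, that every routine TAU admission becomes an SAE, and that the safety comparison favours ICCS by construction. The article does not support that reading, for four reasons.

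- TAU is broader than inpatient care: it is care "which may include inpatient care delivered in the hospital or all other community CAMHS except ICCS".
- The AE condition comes before seriousness, so it is unclear whether a planned admission for an unchanged crisis counts at all.
- No between-arm SAE comparison is specified. Statistical methods {20a} covers the primary and secondary outcomes, and {22} covers recording, review and reporting.
- The direction is not fixed. ICCS participants can be admitted too; equal admission rates give no bias, and higher admission under ICCS reverses it.

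All four points stand, and they limit the claim.

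It can also be said that much is already captured elsewhere. Hospital stay is a secondary outcome, inpatient use is taken from clinical records by proforma, and self-harm has its own questionnaire and model. That is true and makes the fix easier, but it does not change what an SAE total would mean. Finally, the full protocol and the SAP are not shown here, and either may already contain an exemption. If so, the point reduces to aligning the article with it. What remains is a definition that, as printed, does not suit this comparison and that any SAE summary by arm would inherit.

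**Conclusion.** The concern holds as a badly fixed definition. As printed, the SAE criteria do not distinguish psychiatric admission delivered for the index crisis from admission caused by a new or worsened event, so SAE counts by arm can be confounded with treatment setting. If ICCS reduces admissions, which is its purpose, the distortion favours ICCS and can obscure a difference in other harms.

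The size is unknown. Under the assumed admission scenarios with an equal 10% risk of other SAEs, the TAU-to-ICCS ratio runs from 0.67 to 2.22 and is about 2 for 50% vs 20%. These figures rest on assumed admission rates, an assumed and equal background risk, independence of the two, and every admission being counted. No stated estimate or planned efficacy analysis is affected.

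**What to change.** Reconcile {6b} and {22} by stating whether, and when, a psychiatric admission for the index crisis counts as an SAE. In any summary of SAEs by arm:

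- Report psychiatric admissions for the index crisis, and their continuation, on a separate line from all other SAEs.
- Apply the same rule in both arms. Removing only the TAU admissions would create a new asymmetry, this time against ICCS.
- Classify by reason for admission, blind to arm where possible. The setting itself may reveal the arm, so the rule should be written down before classification starts.
- Tabulate deaths, life-threatening events, and hospitalizations for self-harm, overdose or physical illness by arm.

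Expedited reporting stays as it is. The cost is a sentence or two in the safety section and the SAP, plus reclassification of recorded SAEs. The article does not say that the reason for admission is recorded with each SAE; if it is not, it would have to be sought in the clinical records already used for inpatient service use. According to Trial status, recruitment had stopped but follow-up was still under way, so the rule could be set before SAEs are summarized by arm.

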### Frequency and plans for auditing trial conduct {23}

The investigator(s) will grant direct access to source data and other documents to the sponsor(s), REC, authorized representatives of the sponsor, NHS, regulatory authorities, and RECs for trial-related monitoring, audits, and review.

### Plans for communicating important protocol amendments to relevant parties (e.g. trial participants, ethical committees) {25}

We will obtain sponsor approval for all protocol amendments, submit substantial amendments to the REC for written approval, and communicate all amendments to participating NHS Trusts. Amendments will be updated on the clinical trial registry, but not communicated to participants. We will submit an annual progress report to the REC, HRA (where required), sponsor, and funder, and an end-of-study notification and final report to the same parties.

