### Criteria for discontinuing or modifying allocated interventions {11b}

Service user-clinician partnership will tailor interventions to service user needs and preferences as per the engagement approach. Participants have the right to withdraw from the study at any time, without giving a reason. If a participant decides to withdraw, they will be asked on the same day to provide a reason for withdrawal, but they are not required to do so. If a participant withdraws from the study, we will make every effort to report the reason for withdrawal as thoroughly as possible (e.g. adverse events, inability to adhere, inability to attend regularly for treatment or assessment). For participants randomized to the intervention arm, ICCS will be discontinued if they no longer wish to continue, or the trial is terminated at the request of the Data Monitoring Committee (DMC). Randomized participants who wish to withdraw from ICCS will be asked to confirm whether they are still willing to provide study-specific data at a 6-month follow-up and if they wish to participate in the nested qualitative study. It is also possible that the clinical team might withdraw the participant from ICCS if allocated. The reason for a clinician’s decision to withdraw a patient from the study must be recorded and the relevant clinician will clinically assess the participant and arrange appropriate care. Researchers at each site will make every effort to obtain all outcome measures, in priority order, from participants who drop out of treatment as soon as possible. Reasons for and dates of withdrawal from the study will be recorded on a withdrawal form, which will describe the circumstances of the withdrawal. Safety concerns identified through adverse events (AEs) and serious adverse events (SAEs) will be addressed through protocol amendments.

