### Provisions for post-trial care {30}

Participants will remain under the clinical care of the service they are being treated in, which will arrange further treatment or discharge from the service according to their local practices.

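### Safety concerns may be answered by protocol amendment, but the rule that amendments are not communicated to participants has no exception for safety

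*Protocol article*

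**What the plan says.** Two statements in the protocol article bear on this point.

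- Section {11b}, on discontinuing or modifying interventions: "Safety concerns identified through adverse events (AEs) and serious adverse events (SAEs) will be addressed through protocol amendments". The same section gives participants a standing right: "Participants have the right to withdraw from the study at any time, without giving a reason".
- Section {25}, on communicating important amendments. The sponsor approves every amendment, and the trial team will "submit substantial amendments to the REC for written approval" and "communicate all amendments to participating NHS Trusts". It then adds: "Amendments will be updated on the clinical trial registry, but not communicated to participants".

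Three further sections give context. Under Interim analyses {21b}, the sponsor or chief investigator "may prematurely discontinue the trial due to new safety information". Under Adverse event reporting {22}, "Clinical teams will monitor safety throughout the study", and safety reports go to the oversight committees, sponsor, Trust and REC. Under Provisions for post-trial care {30}, "Participants will remain under the clinical care of the service they are being treated in".

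**The concern.** Read together, sections {11b} and {25} mean that one stated way of acting on harm produces a document that, by an unqualified rule, is not sent to the people exposed to that harm. The participants are 12 to 17 years old and in psychiatric crisis, and those under 16 take part with the consent of a person with parental responsibility (Table 1). They may leave at any time, but the value of that right depends on their knowing what bears on the decision.

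The article states this rule; it has not merely left the matter out. If the full protocol carries a safety exception, the article misreports it. If it does not, the rule itself is too broad. What is at stake is participant protection and informed continuation. The treatment comparison is not at stake.

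**Working it through.** The point is textual and the plan gives no figure to reproduce, so the check sets the passages side by side.

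**1. Is amendment a stated response to safety concerns?** Yes, in section {11b}. It is not the only one. The same section allows ICCS to be discontinued if the trial is terminated at the DMC's request, and allows the clinical team to withdraw a participant from ICCS. Section {21b} allows the sponsor or chief investigator to stop the trial.

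**2. Who is told of an amendment under section {25}?**

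| Recipient | What they receive |
|---|---|
| Sponsor | All amendments, for approval |
| REC | Substantial amendments, for written approval |
| Participating Trusts | All amendments |
| Registry | Updated with amendments |
| Participants | Not communicated |

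The section separates substantial amendments from all amendments for the REC and the Trusts, but draws no such line for participants. Its heading concerns important amendments and names trial participants among the relevant parties. It is therefore hard to read the exclusion as covering administrative changes only.

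**3. Does another section supply an exception or a route?**

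- Section {22} lists recipients of safety reports, and participants are not among them.
- Section {30} says participants stay under their service's care, but states no duty to inform.
- Section {21b} foresees new safety information, but says nothing about telling participants.
- No section mentions re-consent, a revised information sheet for enrolled participants, or a notice to families.

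So direct communication is ruled out and no alternative duty is stated. Indirect communication through the Trusts is possible but not required.

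**4. How many people could be affected?** The inputs are the planned sample size of 252 (section {14}), the 36-month recruitment period (Internal pilot) and the 6-month follow-up. Assuming even recruitment over the 36 months:

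- 252 / 36 = 7 per month
- 7 × 6 = 42 in follow-up at any time

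This describes the plan and not the trial as run. Trial status reports that recruitment stopped in September 2023 because the pilot progression criteria were not met. The number recruited is not given. As an illustration only, using the pilot's own 12-month thresholds at an even rate:

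- Fewer than 55 in 12 months: below 55 / 12 = 4.6 per month, so below 55 / 12 × 6 = 27.5 (about 28) in follow-up
- Fewer than 41 in 12 months: below 41 / 12 = 3.4 per month, so below 41 / 12 × 6 = 20.5 (about 21) in follow-up

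**The case against.** The strongest reply has four parts.

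**Families may well hear.** A reader might infer from the two statements that enrolled young people and parents would not learn of new safety information, or could not use their right to withdraw in the light of it. The article does not support that. Trusts receive every amendment, clinical teams monitor safety throughout, nothing bars a clinician from telling a family about a risk, and the REC could require re-consent. Withdrawal needs no reason. This part stands, and the point is limited accordingly. What remains is that none of these routes is stated as a duty.

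**Amendment is not the only safety route.** This also stands. Termination at the DMC's request, withdrawal of a participant by the clinical team and early stopping all act on safety without an amendment. The point concerns only what is handled by amendment.

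**There is no contradiction, and the full protocol may deal with it.** Both statements can be followed as written, and details of re-consent are commonly left to the full document, which section {31c} says is on the funder's website. That would answer a complaint about an omission. It does not answer an explicit, unqualified rule, which the article should state correctly.

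**Little is left to change.** Recruitment has ended and the last follow-up visit was scheduled for February 2024. The wording could matter only for participants still in follow-up, and only if a safety amendment were made; the article reports none. This limits the practical effect but does not make the sentence right.

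**Conclusion.** The point holds in a narrow form. The article makes amendment a stated response to safety concerns, excludes participants from communication of amendments without exception, and states no other duty to inform them or those with parental responsibility. It does not show that safety information would be withheld, and it should not be read that way.

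This is a minor, inexpensive improvement to participant protection, with no bearing on bias, power or the analysis. The figure of about 42 rests on the planned sample size and even recruitment. The number in follow-up in the trial as run cannot be derived from the article and was probably lower. The conclusion does not depend on it.

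**What to change.** Reconcile sections {11b} and {25} in two steps:

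- Limit the exclusion in section {25} to amendments that bear neither on safety nor on willingness to continue.
- State that any other amendment is communicated to current participants and, for those under 16, to the person with parental responsibility, with re-consent where the REC requires it.

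If the full protocol already provides for this, the article's sentence should be corrected to match. The cost is about one sentence of text, plus letters to the families then in follow-up if such an amendment is made. No clinical rule, outcome or analysis changes.
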